#### Stage 1: interventions at hospital

1.1.Individualized discharge education.Patients will be given two face-to-face individualized health education sessions specific to diabetic patients with hypertension by the in-charge nurse. The health education includes health behavior education, disease-associated education and medication education with 15 min for each session. A geriatrics condition screening will also be undertaken using the widely recognized evidence-based screening tool “Fulmer SPICES Comprehensive Assessment Tool for Older Adults” [31]. Education on preventing and managing geriatric conditions will be provided by the in-charge nurse based on the findings from the screening.1.2.Lifestyle modification goals: intervention diary—patient version.1.2.1.Patients will be asked to establish lifestyle modification goals and develop personal action plans with the in-charge nurse. Patients will be provided an “intervention diary—patient version” (Additional file 2) to document their lifestyle modification goals, personal action plans, progress toward the goals, medication adherence, adverse events and unplanned hospital admissions/use of emergency care services.1.2.2.Patients will be asked to discuss and establish their diet plan with the in-charge nurse. The diet plan will be recorded in the “intervention diary—patient version”.1.3.Individualized medication treatment.Prior to discharge, patients will be given an individualized medication treatment plan by the medical specialist. Individualized medication treatment will be recorded in the “intervention diary—patient version”.1.4.Referral to the community health service center: intervention record—community nurse and GP version.1.4.1.When patients are discharged from hospital, they will be referred to a community health service center by the in-charge nurse for regular follow-up over 6 months. An “Intervention record—community nurse and GP version” (Additional file 3) will be sent to the community nurse by the in-charge nurse on discharge to record the required postdischarge interventions and outcomes.1.4.2.In order to establish collaboration and maintain communication among the doctor and nurse at the hospital, the patient and the GP and nurse at the community health service center, a two-way referral letter has been developed (Additional file 4).1.4.3.The in-charge nurse at the hospital will contact the GP and nurse in the community health service center through a telephone call and will fill in the two-way referral letter for patients.1.4.4.The in-charge nurse will help patients to contact the nearby community health service center for the follow-up visit. Patients will be advised of the community health service center they have been referred to, and the name and contacts of the GP and nurse in the community health service center.1.4.5.Data in relation to the patient’s demographic information, pharmacotherapy history and other clinical information will be sent to the community nurse by the in-charge nurse on discharge.1.4.6.Patients will take the referral letter and discharge abstract to the community health service center for the follow-up visit.1.5.Monitoring.The in-charge nurse at the hospital will keep track of the patient’s referral progress through making telephone calls with the patients and community nurses to ensure patients are seen at the community health service center.

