### Usual care

In the usual care group, patients will receive routine discharge education at hospital. After they are discharged, they will go to their usual outpatient clinic of the hospital to receive follow-up and outcome measures at 3 and 6 months. They will not be referred to the community health service center. They will be asked to record the number of adverse events and unplanned hospital admissions/use of emergency care services during 3-month and 6-month follow-up in a usual care table (Additional file 5). The researcher will record the HbA1c and lipid levels close to the 3-month and 6-month follow-up from the patients’ medical record.

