#### Secondary outcomes

Secondary outcomes are the following outcomes at 6-month follow-up adjusted for baseline value: (1) hypertension and diabetes-related health knowledge score measured by a combination of the Hypertension Knowledge-Level Scale (HK-LS) [32] and the Diabetes Knowledge Questionnaire (DKQ) [33]; (2) medication adherence and health lifestyle adherence score measured by the Treatment Adherence Questionnaire of Patients with Hypertension (TAQPH) [34]; (3) HbA1c and lipid values; (4) quality of life score measured by the hypertension scale of the Quality of Life Instruments for Chronic Diseases (QLICD-HY) [35]; (5) the incidence of adverse events and complications associated with hypertension, diabetes, treatments and geriatric syndromes recorded by patients/or carers in the “intervention diary—patient version”; and (6) the incidence of unplanned hospital admissions/use of emergency care services due to uncontrolled hypertension, diabetes and geriatric syndromes recorded by patients or carers in the “intervention diary—patient version”.

Through the study, we hope to identify the challenges that patients face in their hypertension management in the community healthcare settings and to evaluate how to overcome these challenges by improving the capacity of the primary care system. Hence, two open-ended questions will be included for patients upon study completion: (1) Are you satisfied with the follow-up provided by the GP and community nurse in the community health service center? (If not, please explain the reason); and (2) Did you encounter any difficulties of care in the community health service center after discharge? (If yes, please list the difficulties you encountered).

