### Data collection

At baseline, the in-charge nurse will distribute the questionnaires to participants or their family caregiver. They will complete the questionnaires once the consent form is signed and before the individualized discharge education is provided. The patient’s in-charge nurses at the hospital will provide assistance to participants should they have any questions about the questionnaire. Clinical outcomes (BP, HbA1c and lipid values) will be directly recorded from the health record of patients by a research assistant.

At 3-month and 6-month follow-up, community nurses will distribute the questionnaires to participants in the intervention group when they visit the community health service center. Community nurses will be available to assist patients should they have any questions about the questionnaire. In the usual care group, a nurse in the medical specialist clinics will distribute the questionnaire to participants when they visit the outpatient clinic at 3-month and 6-month follow-up. The nurse will be available to assist patients should they have any questions.

Completed questionnaires will be placed in a prepared sealable envelope to maintain confidentiality. The researcher will prepare a drop box in each ward, community health service center and outpatient clinic. Participants will return the sealed questionnaires to the drop box. The research assistants will collect completed questionnaires on a weekly basis.

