### Blinding and allocation concealment

Participants will not know their group allocation during the recruitment and baseline data collection. The research recruiter who is blinded to the group allocation and has no interest in the study will assist the recruitment of participants. Allocation will be disclosed to participants after the baseline data collection. Due to the nature of the study interventions, health professionals who deliver the intervention will know the group allocation during the trial. However, the statistician involved in the data analysis is blinded to the group allocation.

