Previous hypertension management programs in China have been mostly hospital based or community based and only target either pharmacology or nonpharmacology interventions [8, 26]. This is first trial in China to build integrated care based on collaboration and coordination between hospitals and community health service centers to support older people to manage diabetes and hypertension at home using multifactorial interventions. In addition, this study synthesizes the latest evidence and includes the combination of effective intervention components on hypertension management for people with diabetes, which differs from the previous studies in China that only tested single intervention components [44, 45].

The program, if effective, will have an immediate application to hypertension management in the healthcare system in China. In addition, this study uses hypertension and diabetes as an entry point to improve chronic disease management in primary care. Success of this intervention program, that transfers patients from hospital to community health service centers, can also be applied to the management of other chronic diseases for hospitalized patients.

Limitations of this study are the following. First, the trial will be undertaken in 10 clusters only and hence sampling bias may occur, which means that the findings may not represent the population. Second, as an open-label study, the patients and health professionals will be aware of the groups they are assigned to and their allocated treatment during the trial. Patient bias may occur when they complete the self-reported questionnaires. Third, the duration of follow-up at the community health service center is relatively short (only 6 months). The long-term effects of this intervention program will need to be explored in a future study.

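### Secondary outcome (6) counts admissions only for listed causes, as recorded by unblinded patients or carers on different forms, so the cause filter can work differently in the two arms

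*Protocol article*

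**What the plan says.** - **Definition.** Outcome (6), under Secondary outcomes, counts "unplanned hospital admissions/use of emergency care services due to uncontrolled hypertension, diabetes and geriatric syndromes recorded by patients or carers", and names the patient version of the intervention diary as the place of recording. No clinician, record review or adjudicator of cause is mentioned.
- **Intervention form.** Stage 1, item 1.2.1, has patients use that diary for goals, action plans, "progress toward the goals, medication adherence, adverse events and unplanned hospital admissions/use of emergency care services".
- **Usual-care form.** The Usual care section gives these patients a different table: "They will be asked to record the number of adverse events and unplanned hospital admissions/use of emergency care services during 3-month and 6-month follow-up". The sentence does not mention cause.
- **Blinding of the recorder.** "Allocation will be disclosed to participants after the baseline data collection", and the Discussion accepts that "as an open-label study, the patients and health professionals will be aware of the groups they are assigned to".
- **Exposure to the listed causes.** Stage 1, item 1.1, is part of the intervention: "A geriatrics condition screening will also be undertaken using the widely recognized evidence-based screening tool". Teaching on geriatric conditions follows from the result, alongside two individualized sessions on diabetes with hypertension. Stage 2, item 2.2.3, repeats the teaching at monthly visits. Usual care consists of routine discharge education of undescribed content and outpatient follow-up.

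**The concern.** A cause-limited outcome needs a cause filter that works the same way in both arms. Here the filter depends on a lay record made by someone who knows the allocation. The ability to recognise a qualifying cause is also something the program sets out to change: knowledge of hypertension and diabetes is itself secondary outcome (1). The contrast is sharpest for geriatric syndromes. The Background gives falls, incontinence and malnutrition as examples of geriatric conditions. A patient who has been screened for and taught about these is better placed to record a fall-related admission as qualifying than one who has not.

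Different forms add to this, because the article does not say how the cause limit is applied to a number entered in the usual-care table. At stake is whether a difference in recorded admissions, or the lack of one, reflects admissions or labelling. A statistician blinded to allocation cannot repair inputs that were classified differently before the data arrived.

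**Working it through.** The article states no rate, effect or power for outcome (6), so there is no figure to reproduce. The check has two parts.

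**1. The arms side by side**

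| | Intervention | Usual care |
|---|---|---|
| Form described | Patient diary (Stage 1, 1.2.1) | Usual care table |
| Form named in outcome (6) | Yes | No |
| Recorder knows the arm | Yes | Yes |
| Geriatric screening and the teaching based on it | Yes | Not described |
| Hypertension and diabetes teaching | Two individualized sessions, reinforced monthly | Routine discharge education, content not described |
| Clinician asks about events | Monthly assessment by the general practitioner (2.2.4) | Not described; outpatient clinic at 3 and 6 months |

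The recorder is unblinded in both arms. The form and the exposure to the listed causes differ by arm.

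**2. Illustration (every rate below is an assumption)**

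Let p be the risk of a truly qualifying event, s the chance that it is recorded under a listed cause, q the risk of an unrelated unplanned event, and f the chance that it is wrongly recorded under a listed cause. Treating each patient as having at most one kind of event:

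recorded risk = p × s + q × f

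*No true effect, f = 0.* The recorded ratio (intervention/usual care) is s(intervention)/s(usual care). With s = 0.9 in the intervention arm:
- usual care 0.9: 0.9/0.9 = 1.00
- usual care 0.8: 0.9/0.8 = 1.125
- usual care 0.7: 0.9/0.7 = 1.29
- usual care 0.5: 0.9/0.5 = 1.80

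*True risks 15% v 20% (ratio 0.75), f = 0.* The intervention arm records 0.15 × 0.9 = 0.135:
- usual care 0.9: 0.135/0.180 = 0.75
- usual care 0.8: 0.135/0.160 = 0.84
- usual care 0.7: 0.135/0.140 = 0.96
- usual care 0.5: 0.135/0.100 = 1.35

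*Unrelated admissions mislabelled.* Take 30% with any event in both arms, 60% of them qualifying, so p = 0.30 × 0.60 = 0.18 and q = 0.30 − 0.18 = 0.12. Let s be 0.80 v 0.60.
- f = 0 in both arms: 0.18 × 0.80 = 0.144 v 0.18 × 0.60 = 0.108, ratio 1.33.
- f = 0.10 v 0.30: 0.144 + 0.012 = 0.156 v 0.108 + 0.036 = 0.144, ratio 1.08.
- The ratio reaches 1 when 0.108 + 0.12 × f = 0.156, that is f = 0.048/0.12 = 0.40 in usual care. Above that it falls below 1.

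*Scale against sampling error.* With 5 × 25 = 125 completers per arm and a design effect of 1 + (25 − 1) × 0.05 = 2.2 (borrowing the intraclass correlation given for systolic pressure), the 0.144 v 0.108 case has a mean risk of 0.126. The standard error is √(2 × 0.126 × 0.874/125 × 2.2) = 0.062, so 0.036/0.062 is about 0.6 standard errors.

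**The case against.** Several counter-arguments are fair.

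- **Usual care is not without teaching.** These patients get routine discharge education and attend the outpatient clinic. Under the eligibility criteria, every participant already has both diagnoses and was admitted for uncontrolled hypertension and/or its complications. A reader might infer that only intervention patients know the listed causes; the article does not support that for hypertension and diabetes. It does support the contrast for geriatric screening and for structured, repeated teaching.
- **The forms are not shown.** Additional files 2 and 5 may contain a cause field, and the article's description of the diary mentions no cause either. A reader might infer a cause-limited count in one arm set against an all-cause number in the other. Under the 30% and 18% assumed above, that would give 0.18/0.30 = 0.60. The text does not establish this, so it should not be offered as the expected size. A cause field would not remove the concern, because an unblinded lay person would still fill it in.
- **Recording is not the same as deciding.** A patient might copy a stated diagnosis, and in the intervention arm the general practitioner reviews events monthly. The article does not name that review as the source for outcome (6) and describes no counterpart in usual care, so it may lessen lay mislabelling in one arm while leaving the arms unequal.
- **The limitations are acknowledged.** The Discussion admits patient bias, but only for the self-reported questionnaires.
- **The illustrated shift is small against noise.** This is true: about 0.6 standard errors in the case worked, and allowing some unrelated admissions to be mislabelled can shrink or reverse it.

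**Conclusion.** The concern holds in a limited form. Followed as written, the plan applies a cause filter that can work differently by arm, because an unblinded lay recorder, unequal exposure to the listed causes and different forms coincide. This is not detail left to another document: the article fixes the cause limit, the recorder and the form.

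The size and direction of the bias cannot be determined from the article. The illustrative ratios rest wholly on assumed admission and labelling rates, and they show only that a null effect could look harmful and a true benefit could be masked. They do not show that the result will be wrong or in whose favour. A reader might conclude that outcome (6) would be uninterpretable; that goes too far. It would be open to a labelling explanation that the analysis could not exclude.

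Outcome (6) is one of six secondary outcomes with no power claim, and the primary comparison of systolic blood pressure is untouched. The change is a worthwhile, low-cost improvement rather than a condition for the trial to proceed.

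**What to change.** **Change.** In Stage 1 (item 1.2.1), Usual care, and Secondary outcomes (6):
1. Have patients or carers in both arms record every unplanned admission or emergency visit, with date and site, on the same form, without judging its cause.
2. Compare the arms on that count regardless of cause. The Abstract already describes this outcome as unplanned readmission with no cause limit.
3. Report the cause-specific count as supporting. Existing study staff would code cause from the discharge or emergency record against one list of qualifying diagnoses, without seeing the arm label.
4. Show events with no retrievable record as cause unknown, by arm.

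**Cost.** Wording in three places and one shared form. The all-cause count is less specific to what the program targets. Record retrieval is some new work: under Data collection, the statement that clinical outcomes "will be directly recorded from the health record of patients by a research assistant" concerns baseline blood pressure, HbA1c and lipids, and the Usual care section adds only HbA1c and lipids near 3 and 6 months. Retrieval may be incomplete outside the study hospitals. Recruitment is already under way, so a new form reaches only patients still in follow-up; cause can be coded retrospectively for the others. The change removes the arm-dependent cause filter. It does not by itself guarantee that events are reported equally completely in both arms.

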### Sample size

The sample size calculation is based on the primary outcome and is estimated on the basis of an earlier randomized controlled trial study in relation to hypertension management for diabetic patients [36]. In this earlier study, the researchers found a 7.3 mmHg significant reduction in systolic blood pressure (SBP) with a standard deviation of 12.1 mmHg and an intraclass correlation coefficient (ICC) of 0.05 in the intervention group [36]. Since randomization in our study will be done by wards (clusters), the sample size has been adjusted to take into account the design effect. Our study is designed to have 80% power to detect a difference of 7.3 mmHg SBP between the group means when the standard deviation is 12.1 mmHg. This assumes that a sample size of five clusters per group with 25 participants per cluster will complete the study and the ICC is 0.05, giving a design effect of 1.48. The ICC also reflects the situation that the hospitals in the study are from the same city under the same hospital administration standard; therefore, each cluster is unlikely to differ from the others with respect to the variable of interest. Each cluster will be of equal size. Assuming an attrition rate of 10%, we would require 27 participants per cluster. In total, 10 clusters with 270 participants will be recruited.

### Participant recruitment

Recruitment posters will be presented in the patient activity rooms in the participating wards. An information pack including an information sheet, consent form and other study-related documents (i.e., intervention diary—patient version; usual care table) will be displayed on a table placed under the poster for potential participants to view. Potential participants will be asked to return their decision on participation via a response slip to a drop box in each participating ward. On receiving the response slip, a research recruiter who is blinded to the group allocation and has no interest in the outcome of the study will contact the patients to confirm their eligibility to participate. One of the project team members, who will know the allocation, will provide detailed information related to the study and have the participants sign the consent form. Although the allocation will be known to the project team member, the risk of selection bias and influences on the measure of baseline outcome will be minimal because the participants will have been identified and recruited by the research recruiter rather than the project team member. Participants will be informed that refusal to participate in this study will not alter the caring relationship between them and the hospitals. Participants will be reminded that they can discontinue participation in the study at any time without any influences on their usual care.

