### Randomization

Participants will be recruited from hospitals and continue the trial at community health service centers. Randomization will be performed based on the ward clusters rather than participants. Health professionals involved in the study practice are in a single ward only, therefore the chance of contamination between intervention and usual care wards in the same hospital is very low. There are six secondary hospitals and five tertiary hospitals that provide in-patient care for patients with diabetes and hypertension in Nanchang. As part of the ethics application processes, researchers in the project sent out invitations to all of these 11 public hospitals in Nanchang and informed them that two secondary hospitals and two tertiary hospitals would be randomly selected. The number of hospitals to be included in the trial was estimated on the sample size calculation. In total, six secondary hospitals and five tertiary hospitals agreed to participate. To ensure the selected hospitals are representative of the hospitals in Nanchang, two hospitals will be randomly selected from each level. There are two eligible wards in each participating secondary hospitals and three eligible wards in each tertiary hospital. To ensure the selected wards are representative of the wards in each level of the selected hospitals, three wards from tertiary hospitals and two wards from secondary hospitals will be randomly assigned to either an intervention group or a usual care group. The group assignment will be undertaken by a PhD fellow who is not involved in the trial and is blind to the wards. Patients who meet the inclusion criteria in these participating wards will be invited to the trial. There are six community health service centers that provide chronic disease management for residents in Nanchang. The invitations were sent to these community centers and all of them agreed to participate in the trial. A flow chart of the randomization is shown in Fig. 3.

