### Quality control procedures

Quality of data collection will be ensured during the whole study phases. Two 1-h workshops and ongoing support at each participating site will be provided to the health professionals to allow them to discuss, understand and follow the study protocol. Research assistants will be employed to distribute and collect the questionnaires. Consent forms, questionnaires and other data collection documents will be checked for completeness. Data at three time points (baseline, 3-month and 6-month follow-up) will be checked using the birth date of patients to ensure the data are matched correctly. The quality of the study will be overseen by the PhD supervision team and the representative of the Department of Scientific Research Management at Health and Family Planning Commission of Jiangxi Province, China. The data entered into SPSS will be checked to prevent input errors by the other two PhD fellows who are not involved in this study. The compliance of patients with the interventions will be optimized by a telephone call from the nurse at the community service center to remind them of the follow-up visits at the community health service center.

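### Study information and consent are handled by someone who knows the ward's arm, so the minimal-risk statement on selection bias is unsupported; two sections also disagree on who hands out baseline questionnaires

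*Protocol article*

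**What the plan says.** Allocation is by ward: "Randomization will be performed based on the ward clusters rather than participants" (Protocol article, Randomization). Patients come afterwards: "Patients who meet the inclusion criteria in these participating wards will be invited to the trial" (same section).

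Participant recruitment then describes three steps. A patient drops a response slip into a box on the ward. A recruiter blinded to allocation contacts the patient to confirm eligibility. The last step is not blinded: "One of the project team members, who will know the allocation, will provide detailed information related to the study", and the same person obtains the signature. The section concludes that "the risk of selection bias and influences on the measure of baseline outcome will be minimal", because the recruiter rather than the team member has identified and recruited the participants.

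Blinding and allocation concealment states that "Participants will not know their group allocation during the recruitment and baseline data collection". It mentions the blinded recruiter but not the unblinded person who takes consent.

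On baseline questionnaires, Data collection says: "At baseline, the in-charge nurse will distribute the questionnaires to participants or their family caregiver". The same nurse answers questions about them. Quality control procedures says: "Research assistants will be employed to distribute and collect the questionnaires".

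**The concern.** In a cluster trial that allocates wards first, concealment at randomization does not protect individual enrolment. Whoever explains the study and takes the signature should not know the arm. Otherwise encouragement, emphasis or discouragement can differ between arms, and so can the kind of patient who enrols. Baseline adjustment removes only the part of such a difference that the measured covariates capture; motivation, for example, is not among the listed adjustment variables.

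The article does not leave this step to a fuller document. It says that the person is unblinded, and then gives an assurance that its own description does not support. The limitations listed in the Discussion do not mention the risk.

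The questionnaire issue is a different one. It concerns how baseline self-report is measured, not who enters the trial. It matters because the knowledge, adherence and quality-of-life outcomes are all adjusted for their baseline values.

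**Working it through.** The article gives no figure for this risk, so the main check is a comparison of the text.

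**Consent**

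1. *Order.* Wards are assigned, then patients in those wards are invited (Randomization). The arm is thus fixed and knowable when each patient is approached.
2. *Recruiter's stated task.* Contact patients who returned a slip and confirm eligibility (Participant recruitment). No other contact with patients is specified, although Blinding and allocation concealment says in general terms that the recruiter assists recruitment.
3. *Team member's stated task.* Give the detailed information and obtain the signature, knowing the allocation (Participant recruitment).
4. *The reason given for minimal risk.* Participants have already been recruited by the recruiter. Under steps 2 and 3 a patient at that point has returned a slip and been found eligible, but has neither had the detailed explanation nor consented. The reason conflicts with the sentence before it.
5. *What remains exposed.* Loss between slip and signature. One possible route: unwillingness to return to a community health service center is an exclusion in both arms (Eligibility), yet usual-care patients are not referred there (Usual care). Someone who knows the arm could present that requirement differently by ward. The article does not say that this happens.

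**Baseline questionnaires**

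1. The in-charge nurse distributes and assists (Data collection). In intervention wards this nurse gives the discharge education (Stage 1), and those who deliver the intervention know the arm (Blinding and allocation concealment).
2. Research assistants distribute and collect (Quality control procedures). The two statements cannot both describe who distributes at baseline.
3. Baseline blood pressure, HbA1c and lipids are taken from the health record by a research assistant (Data collection). The nurse's role therefore cannot reach baseline systolic pressure; it can reach only the questionnaire scores.

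**Scale, for orientation only**

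Inputs from Sample size: difference 7.3 mmHg, SD 12.1 mmHg, five wards per arm, 25 completers per ward (125 per arm), ICC 0.05, power 80%. The 5% level is from Statistical methods; a two-sided test is assumed.

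- Variance inflation: 1 + (25 − 1) × 0.05 = 2.20. The article prints 1.48, which is a separate matter. I use 2.20 because it reproduces the stated power.
- Effective size per arm: 125 / 2.20 = 56.8. Standard error of the difference: 12.1 × √(2 / 56.8) = 2.27 mmHg.
- Power for 7.3 mmHg, noncentral t with 10 − 2 = 8 degrees of freedom: 80.4%, in line with the stated 80%.
- With no true effect, if selective consent left a residual shift of 1, 2 or 3 mmHg in the adjusted comparison, the test would reject about 7%, 12% or 21% of the time instead of 5%.

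The shifts are assumptions. Nothing in the documents says which of them, if any, applies.

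**The case against.** The strongest reply is that the pool is formed without knowledge of the arm. Patients return the slip before any study contact described in the article, and a blinded recruiter screens them. Participants are to learn their allocation only after baseline collection, so differential consent requires the team member to disclose the arm or persuade selectively, and the plan describes neither. Questionnaires are completed before the education and returned sealed. The information pack lists both the intervention diary and the usual care table and is not said to differ by arm.

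All of this stands, and it narrows the point. It does not rescue the stated reason, because the slip precedes the detailed information and the signature, and both of those are unblinded.

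Three stronger readings are tempting, and the documents do not support them:

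- *That recruitment bias will occur, or that patients have no protection at all.* The slip and the blinded eligibility check are real safeguards; what is missing is protection at the last step.
- *That the nurse's questionnaire role adds to recruitment bias or distorts the primary outcome.* It is a measurement question, the nurse distributes and assists rather than administers, and baseline systolic pressure comes from the record.
- *That the bias can be sized.* Assuming a shift of 0.1 to 0.3 SD gives 0.1 × 12.1 to 0.3 × 12.1 = 1.2 to 3.6 mmHg, or 17 to 50% of 7.3 mmHg. That range has no basis in the documents, and it uses the full SD although the model adjusts for baseline and seven further covariates.

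**Conclusion.** The point holds in a limited form. Protection against differential consent between slip and signature is not secured, and the claim of minimal risk is unsupported because its reason contradicts the procedure just described. This rests on the article's own wording and needs no outside assumption.

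Separately, Data collection and Quality control procedures disagree on who distributes the baseline questionnaires. If the in-charge nurse does so, baseline knowledge, adherence and quality-of-life scores in intervention wards are collected with help from someone who knows the arm.

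The size and direction of any bias cannot be derived from the documents. The rejection rates above show only how sensitive the primary test would be if a shift existed. The weakness should be corrected where it still can be and made visible in reporting; it does not show that the result will be biased.

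**What to change.** 1. For remaining recruitment, have the existing blinded recruiter give the detailed information and take consent in every ward, with the same pack and a uniform script. The team member who knows the allocation meets participants only after baseline is complete.
2. Reconcile Data collection with Quality control procedures: research assistants, not the nurse who delivers the intervention, distribute and assist with baseline questionnaires. The article does not describe these assistants as blinded, so state that they are kept unaware of the ward's arm as far as possible.
3. Remove the minimal-risk statement from Participant recruitment.
4. Report slips returned, patients eligible, consented and refused, by ward and arm, separately before and after the change.

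*Cost.* No new staff, but a little more of the recruiter's time. Trial status says that recruitment was under way at submission, so the change leaves two consent procedures within the trial; the before-and-after reporting in item 4 is there for that reason. If recruitment has closed, items 3 and 4 still apply, with item 4 as a single count, and the report should say who in fact distributed the baseline questionnaires.
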